### Ethics and Dissemination

Manchester Metropolitan University Ethics Committee approved this study on 29/09/2020 (Ref: 25307). Informed consent will be gained from all participants prior to referral onto the rehabilitation programme. Consent will be captured digitally as part of the online referral programme.

Participants will be contacted weekly to ensure that any clinical concerns are addressed and escalated where relevant. Processes are in place to inform the referring clinician and the participants general practitioner should medical intervention be required.

The principal investigators will have access to the cleaned data sets. Project data sets will be housed securely within the project database hosted on a secure Nuffield Health server. Should data sharing be required under reasonable request (e.g., with the NHS) a secure file transfer protocol will be created for the study, and all data sets will be password protected. To ensure confidentiality, data dispersed to project team members will be blinded of any identifying participant information.

Pilot data is expected by December 2021 and will be published in an open access journal. Any intellectual property pertaining to successful delivery of the service will be shared directly with NHS partners.

## Discussion

New models of rehabilitation are urgently required to address the immediate gap in provision for those recovering from COVID-19 as well as the escalating back log of rehabilitation cases nationally. Nuffield Health, the UK's largest not-for-profit healthcare charity, have long prioritised exercise as a first line intervention for the treatment and prevention of long-term conditions. This has been successfully achieved via a uniquely structured estate linking hospitals and health and well-being centres as well as the up skilling of exercise professionals to work with clinical populations. Now, by working closely with the NHS, a unique learning partnership will assist in the development of a new rehabilitation pathway, that may later evolve to utilise the expertise of the fitness sector in supporting the NHS and its rehabilitation needs. We must also later review in detail how we create a model that has utility beyond the healthcare system within the United Kingdom, such that patients are able to benefit from this level of support internationally, within varying healthcare structures.

Undertaking the principal aim of this trial will allow for a robust test of the effectiveness of a new 12-week blended rehabilitation programme within a population that has not previously been investigated within a community rehabilitation context. Specifically, this work will provide new insight into changes in HR-QoL and disease specific symptoms related to COVID-19 following 12-weeks of exercise rehabilitation. Positive results of these main outcome measures will allow the programme to consolidate itself as not only a valid treatment option, but as an essential component to the care management pathway of COVID-19 survivors, and indeed those recovering from other serious conditions.

The novel structure of the programme will support further expansion of digital components within the rehabilitation of those recovering from serious illness. This is relevant not just for improving access to information and efficiency of data collection but critically, the remote delivery of care and the ability to individualise programmes of rehabilitation. The relevance of the results will likely have implications for the implementation and success of blended rehabilitation models i.e., digital and physical combined, across health care systems worldwide.

Examining potential mediators and moderators of change will contribute to our understanding of key processes in achieving improvement in services using blended models of rehabilitation. Whilst mediators and moderators of rehabilitation outcomes have been explored, this will be the first exploration of a combined digital/physical intervention. This will inform the tailoring of interventions to best address the needs of the targeted population, ultimately leading to the development of more effective interventions.

An area requiring on-going review and indeed development relates to the provision and impact of rehabilitation across sociodemographic groups. Black, low-income, and immigrant communities are particularly vulnerable and disproportionately impacted by COVID-19 (36, 37). Furthermore, data exists indicating that secondary care-based clinics may be underused by older populations and those in poorer socioeconomic circumstances (37). The proposed evaluation will ensure that sociodemographic variation is considered within analysis and that a representative sample from those that are disproportionately affected are consulted post-programme to understand barriers and facilitators. It is critical that learnings are continuous and that they are built into future re-iterations of the rehabilitation programme.

The proposed economic analysis will add to the current literature in regard to evidence of the cost-effectiveness of home or web-based rehabilitation programmes and will be an innovative analysis of a clinical rehabilitation programme ran independently of allied health professionals within a non-NHS community environment. In a context of health care provision where resources are now especially stretched, cost-effective interventions can only support the delivery of effective health services.

In summary, COVID-19 has proven devastating in its cost of life and long-term impact on survivors. Scalable interventions must be developed to address what will be a long-term requirement in the rehabilitation of patients having suffered critical illness. To achieve rapid scalability, blended interventions will soon become a recognised viable option across health care. They can be beneficial both in costs and resource management within the NHS and will bring disparate sectors closer together in a combined mission of improving the health of the nation. It is critical that as technology rapidly develops, supporting innovative models of care so too must research in order to rapidly continually and rapidly update on the benefits of providing blended community rehabilitation. This long-term evaluation aspires to drive research and innovation forward, and in doing so support the NHS in its aim of controlling the impacts of COVID-19 and delivering on its long-term plan.

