## Methods and Analysis

### Trial Design

The protocol presented herein reflects Protocol Number 01. Any amends to this protocol will be detailed in full within the ISRCTN registry. This observational cohort study will be conducted following the STROBE statement (25) for observational studies with the protocol reported in line with SPIRIT Statement (26). We will examine the effectiveness of a 12-week blended community rehabilitation programme on improvements in HR-QoL and reductions in symptoms of COVID-19, in individuals recovering from the disease.

This evaluation will be conducted in concert with the NHS. Initially the programme will be deployed across 4 NHS locations, namely; University Hospitals of North Midlands Trust, Newcastle upon Tyne Hospitals NHS Foundation Trust; Birmingham and Solihull Community Care Group and Central Manchester University Hospitals Trust. Whilst these locations are clustered in the North and Midlands they are demographically and economically diverse. The NHS sites will be serviced by 8 surrounding Nuffield Health Fitness and Well-being Centres, all of which are registered with the Care Quality Commission and are located within a 20-mile radius of a participating NHS site. Each trust will be assigned 2 rehabilitation specialists from Nuffield Health to support the programme. As this intervention will be offered as a National service, recruitment is open ended beginning in September 2020. Nuffield Health intend to expand provision by operationalising all 112 of its fitness and well-being centres in 2021. These locations cover all 7 geographical regions as defined by NHS criteria. An initial evaluation cohort will not exceed 160 participants ensuring that a participant practitioner ratio of 1:10 is not exceeded.

Those wishing to access the programme can do so via NHS referral, this can be through doctor, nurse or other allied health professional such as a physiotherapist. Patients will only be referred if they meet the qualifying criteria presented in Table 1.

**Table 1 T1:** Inclusion and exclusion criteria.

**Inclusion criteria**	**Exclusion criteria**
Previous diagnosis of COVID-19	Active COVID-19 symptoms
Able to walk independently for a minimum of 20 m	Are already receiving community rehabilitation
Must have access to the internet and smartphone/tablet/personal computer (with adequate technological literacy)	Have un-managed medical conditions that contraindicate unsupervised exercise

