18 years of age and over	Have a formal diagnosis of post-traumatic stress syndrome, clinically significant anxiety or depression where low intensity mental health intervention will not assist
Access to transport for phase 2 attendance	Have been diagnosed with Chronic Fatigue Syndrome

Once referred, the patient will complete an online pre-assessment health questionnaire. Once completed the questionnaire is made available digitally to a specialist trained physiotherapist who will contact the patient to conduct a telephone triage assessment. Following successful triage, the patient is handed on to a rehabilitation specialist who then takes up responsibility of the patients care. All patients will receive the identical 12-week programme structure consisting of two 6-week phases, depicted in Figure 1 and described in detail below.

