### Rehabilitation Programme

NHS healthcare professionals will utilise inclusion/exclusion criteria at the point of discharge to refer a patient to the programme. Alongside the provision of a patient information document, the patient will be fully informed verbally about the programme, being given the opportunity to join the programme should they so wish. The patient will be made aware that their data will be utilised anonymously for research purposes. The patient may also request that their data is not utilised and will still be able to participate in the programme. Should they choose not to progress they will be sign-posted to alternative community/NHS services where available. If the patient accepts to progress on to the programme the NHS healthcare professional will complete an online referral, sent directly to Nuffield Health using a secure online form. Data sharing agreements have been completed between NHS and Nuffield Health and all processes conform to GDPR and NHS digital requirements.When an online referral is completed, an automated booking process is triggered. Via email or telephone (based on patient preference) the patient will choose an appointment time for an initial triage screening. The patient will also be asked to complete pre-screening questions, designed to support the triage process.The patient next joins a telephone or online video triage consultation utilising this feature. The triage is conducted by specialist physiotherapists trained in remote consultation. The triage is designed to be an additional safety step ensuring that the patient is clinically fit to progress onto the 12-week programme. The 45-min triage will also act to collect additional relevant patient information that may be pertinent when tailoring their exercise programme. Information such as details on additional co-morbidities, emotional well-being and medication will be discussed. Should any contraindications to exercise be identified during the triage the patient will be informed that they are unable to progress on the programme at that time. The patient will be sign-posted back to their General Practitioner, who will also be notified in writing. The original referring clinician will also be notified. At the end of triage, if deemed appropriate, the specialist physiotherapist will refer the patient to the rehabilitation specialist with recommendations for the intensity of entry level exercise and specific needs and goals.Following successful triage, the patient will be automatically sent a welcome pack via post as well as email. This will provide full guidance on how to download, access and register on the digital platforms and will provide links to learning materials. The patients GP will also be made aware that their patient has initiated the programme. The digital application platform utilises the functionality of a platform already used extensively across Nuffield Health (MyTherapy, Nuffield Health, London, UK). All other virtual audio-visual communication will be delivered by a separate digital system (Microsoft Teams, Microsoft, Redmond, USA).Within 72 h of referral, the patient will be contacted by their assigned rehabilitation specialist based at a Nuffield Health site within a 20-mile proximity to the referring hospital. practitioner will provide a welcome to the programme, offer the opportunity to ask any questions and to inform them of the start date of the programme.The patient begins the 12-week programme. This programme phases are as follows:

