### Patient and Public Involvement

Patients were first involved in this evaluation at their point of clinical referral following a 12-week post discharge follow up. The research questions posed within the protocol paper were constructed with the support of NHS clinicians whom work directly with this clinical population as well-members of NHS Trust management. We believe that the research questions reflect the immediate and on-going needs of the NHS who have a strong insight as to their patient's needs.

Qualitative feedback will be collected from patients throughout their rehabilitation. An initial cohort of 100 patients will be invited to review each milestone of the programme as part of a focus group following their rehabilitation. An evaluation period will then be employed to refine the pathway based on patient feedback, this will include feedback on outcome and recruitment methods.

A patient survey will be provided to all participants that were eligible for the rehabilitation programme gauging views on the dissemination plan and how the intervention may further integrate into community settings.

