## Measures

Outcome data will be collected at 0, 6, and 12 weeks and again at 6- and 12-months post-intervention. Self-report data will be collected via digital application (MyWellbeing, Nuffield Health, London, UK). The patient will be emailed and provided a push-notification prompting them to complete the aforementioned questionnaires. Whilst this evaluation will not utilise any formal comparison group, it is intended that collaboration with trusts will support the analysis of anonymised “usual care” outcome data. This is likely to come from community physiotherapy and/or modified pulmonary rehabilitation.

All data will be securely stored on a dedicated Nuffield Health server and will be retained in line with the organisations publicly available data retention schedule. Modifications to data written to the database will be documented through via an internal inquiry system. Data entered into the database will be retrievable for viewing throughout by those granted secure access privileges associated with an identification code and password. Any data errors will be summarised along with detailed descriptions for each specific problem in a data query reports, which will be sent to the study Outcomes Analyst. The Outcomes Analyst will check any inconsistency, checking other sources to determine required corrections. Any coding changes required within the digital data capture system will then be implemented within 24 h.

Complete back up of the primary database will be performed twice a month. Incremental data back-ups will be performed on a daily basis. In addition to system back-ups, additional measures will be taken to back-up and export the database on a regular basis at site level. The outcomes analyst will send weekly email reports with information on missing data, missing forms, and missing visits to site level co-ordinators who will then rectify immediately as and when required. Data security audits will be completed by the Nuffield Health Information Security group on a quarterly basis. Full details of group membership and details of audit processes can be provided upon request.

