### Statistical Analysis

Participation levels will be monitored throughout the programme and reasons for withdrawal or non-compliance will be recorded. All participants are selected according to clinical criteria alone with no other factors influencing participation so as to limit selection bias. Information biases are limited via the prospective nature of this evaluation and the methodology employed to collect mandatory data at each designated time point. As well as the primary and secondary outcome measures being collected, a detailed clinical history and additional triage will be undertaken for each participant. This will limit confusion bias through the identification of relevant confounding clinical variables. Efficacy of treatments over time will be measured using mixed effects models. To complement the *post-hoc* comparisons, the magnitude of change on the primary and secondary outcomes measures will be established using Cohen's *d* statistic. Bonferroni corrected *p*-values will be reported for multiple comparisons. Participants with missing data will be removed for analysis with complete-case analysis being utilised.

An interim-analysis will be performed on the primary endpoint when 50% of participants have completed up to the 6-month follow up point. The interim analysis will be performed by an independent statistician. The statistician will report to the principal investigator ([name]) only. The principal investigator will have unblinded access to all data and will discuss the results of the interim analysis with the project team.

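### A single-arm before-after cohort is presented as a robust test of effectiveness, although natural recovery could produce the same change; separately, the protocol gives two conflicting referral times

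*Protocol article*

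**What the plan says.** **Design.** Under Trial Design the protocol states "This observational cohort study will be conducted following the STROBE statement" and "All patients will receive the identical 12-week programme structure consisting of two 6-week phases". The Measures section adds "Whilst this evaluation will not utilise any formal comparison group". It also records an intention to analyse anonymised usual-care outcomes from the trusts, probably from community physiotherapy or modified pulmonary rehabilitation. The Statistical Analysis section does not mention that comparison.

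**Analysis.** Efficacy is to be measured over time with mixed effects models, supplemented by Cohen's d and Bonferroni-corrected p-values, on complete cases. On confounding, the protocol relies on the clinical history and triage: "This will limit confusion bias through the identification of relevant confounding clinical variables".

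**Claims.** Hypothesis (a) in the Aims is that the programme will be effective for quality of life and symptoms at 6 and 12 weeks, with benefits kept at 6 and 12 months. No comparator is named for it. The Discussion says "Undertaking the principal aim of this trial will allow for a robust test of the effectiveness of a new 12-week blended rehabilitation programme" and continues "Positive results of these main outcome measures will allow the programme to consolidate itself as not only a valid treatment option", going on to call the programme indispensable to the care pathway. The strengths and limitations list gives self-reporting as a weakness. It mentions neither the missing control group nor natural recovery.

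**Timing.** The Rehabilitation Programme section says "NHS healthcare professionals will utilise inclusion/exclusion criteria at the point of discharge to refer a patient to the programme". The Patient and Public Involvement section says "Patients were first involved in this evaluation at their point of clinical referral following a 12-week post discharge follow up".

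**The concern.** The only planned estimate is the change in one treated group. People discharged after COVID-19 may improve on EQ-5D-5L and Dyspnea-12 without any programme, and a before-after comparison would count that improvement as benefit. The protocol's interpretation leaves no room for this, because a positive change on the main outcomes is to establish the programme as a treatment. The stakes are considerable, since the protocol plans to extend provision to all 112 centres.

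The referral conflict is a second, separate problem. If week 0 may fall soon after discharge or about 12 weeks later, a reader cannot judge how much recovery was still to come when measurement began.

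**Working it through.** **1. Does the design support the claim?** Every participant receives the same programme, there is no concurrent control, and the estimate is a within-cohort time effect. The expected change at a visit is

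E(change) = programme effect + natural change over the same interval.

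Only the sum is estimated, and nothing in the planned data identifies the two parts.

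**2. Do the stated safeguards help?** Clinical history consists of covariates fixed at baseline. They can explain why participants differ from one another, but time since illness advances equally for everyone and is aligned with exposure to the programme. Adjusting for history therefore leaves the shared trend in place. Bonferroni correction limits chance findings and does not touch bias.

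**3. How large could the effect be?** The protocol has no power calculation, effect size or SD, so there is no figure of its own to reproduce. The following is an illustration.

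Inputs:
- n = 160, the cap on the initial cohort (Trial Design)
- programme effect = 0 (assumed)
- natural change d = 0.1, 0.25 or 0.5 SD of the change score (assumed)
- alpha = 0.05, or 0.05/8 = 0.00625 for 2 primary outcomes × 4 follow-ups (assumed count), with critical values 1.960 and 2.734

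Formula, two-sided paired normal approximation:

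P = Φ(d√n − z) + Φ(−d√n − z), with √160 = 12.649.

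| d | d√n | P at 0.05 | P at 0.05/8 |
|---|---|---|---|
| 0.1 | 1.265 | 0.24 | 0.07 |
| 0.25 | 3.162 | 0.885 | 0.67 |
| 0.5 | 6.325 | >0.999 | >0.99 |

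For d = 0.25: Φ(3.162 − 1.960) = Φ(1.202) = 0.885, and Φ(3.162 − 2.734) = Φ(0.428) = 0.67.

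The smallest observed change that reaches significance is z/√n: 1.960/12.649 = 0.155 SD, or 2.734/12.649 = 0.216 SD after correction.

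Complete-case analysis, and the patient's right to withhold data, will lower n. With n = 100 (assumed) and d = 0.25, d√n = 2.5, giving Φ(0.540) = 0.71 and Φ(−0.234) = 0.41.

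**4. Timing.** One passage has staff referring at discharge. The other has patients first involved at a referral that follows a 12-week post-discharge follow-up. Both concern referral, and neither defines week 0. The Rehabilitation Programme section has the specialist call within 72 hours of referral to give the start date, but sets no interval to that date. By inference, week 0 moves with referral and could differ by about 12 weeks between the two readings.

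**The case against.** The strongest reply is that nothing is hidden. The protocol calls itself an observational cohort, says there is no formal comparison group and hopes to use usual-care data. The sentence after the robust-test claim speaks more modestly of insight into changes in quality of life and symptoms. Hypothesis (a) is demanding, since it covers both outcomes at several times, and no rule makes one significant p-value the criterion of success. All of this is fair. It shows that the design is disclosed, but hypothesis (a) and the Discussion still draw a conclusion that the disclosed design cannot give.

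The usual-care data do not repair this. They are only an intention, without a settled source or analysis. If they come from the services named, they describe other active rehabilitation and not untreated recovery.

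Four stronger readings are tempting, and the protocol does not support them:
- **The timing conflict causes the misattribution.** It does not. The missing control does, and would do so even if the two passages agreed. The conflict only obscures the likely size of the bias.
- **An ineffective programme would usually appear effective.** That depends on an unknown recovery rate. At 0.1 SD the probability is 0.24, or 0.07 after correction. The Introduction itself cites impaired quality of life for up to 14 months after MERS.
- **Regression to the mean adds to the bias.** Table 1 sets no entry threshold on either primary outcome, so there is no documented selection on poor scores.
- **Baseline scores plotted against days since discharge would give the untreated recovery curve.** Patients referred later may differ because their problems persisted, so a cross-sectional gradient is not a valid counterfactual.

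**Conclusion.** The concern holds in this form: the protocol attributes to a single-arm before-after cohort the ability to test effectiveness robustly, which the design does not have. Natural recovery could be credited to the programme, and the listed safeguards do not prevent it. This follows from the design alone and needs no numerical assumption.

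Its size cannot be determined from the protocol. The probabilities above, from 0.24 to above 0.999 uncorrected and from 0.07 to above 0.99 at 0.05/8, rest on assumed natural change of 0.1 to 0.5 SD, a single comparison, no programme effect and the full cap of 160.

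The conflict over referral time is a separate inconsistency. It bears on week 0 only by inference, but it leaves the likely size of the bias unclear.

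**What to change.** 1. Restate the aim, hypothesis (a) and the Discussion as change from baseline in programme participants. Delete the robust-test claim and the inference that positive results make the programme an indispensable part of care. Add the missing control group and natural recovery to the strengths and limitations list.
2. Reconcile the referral statements in the Rehabilitation Programme and Patient and Public Involvement sections. Record days from discharge to week 0, and put this and its interaction with assessment time into the mixed model. Present the result as a description of how change varies with time since discharge, not as a correction for natural recovery. If all patients enter at nearly the same time, the term will tell little, but the recorded dates will still show readers where week 0 lies.
3. If a usual-care comparison is made, label it as a comparison with other active rehabilitation. Adjust for baseline score and time since discharge where the trusts can supply them; the protocol promises only anonymised outcome data. Do not present it as evidence against untreated recovery.

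Items 1 and 2 cost rewording, one date field and one covariate with its interaction, with no new arm. The real price is a less favourable headline claim. Item 3 depends on what the trusts can provide.
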